### Patient recruitment process

A study clinician will review a list of potentially eligible patients (with stage III melanoma) obtained from the MIA Melanoma Research Database to check clinical eligibility (ie, are still under the care of MIA clinicians at either site or have not progressed to stage 4 melanoma). Updated lists will then be sent to each of the treating clinicians who will be able to remove patients they feel are not appropriate to invite to participate in the study for other reasons. The clinical nurse consultant or clinic secretary will then send the approved list of eligible patients to the project officer.

These patients will be initially contacted by the project officer prior to their scheduled clinical review appointments. The project officer will send them three documents along with a covering letter (either by email or post; posted documents will contain a stamped self-addressed envelope). The email/letter will briefly introduce the study, ask patients to read the invitation to participate and the participant information statement (PIS), and to complete and return an EoI form, which provides patients with three options to select from: willing, potentially willing or not willing to participate. If patients do not respond to the request to return the EoI, the project officer will telephone them once to check whether they have received it.

The project officer will follow up those patients who have indicated their willingness or potential willingness to participate, answer any questions and concerns they may have about the study and ask them to arrive 30 min earlier for their scheduled appointment to allow time to complete the questionnaires. The PIS contains contact numbers of the academic and clinical leads for this project so patients may contact them prior to making their decision to participate. When patients arrive at the clinic for a regular appointment, they will again be given the opportunity to discuss any questions they may have regarding their participation with the project officer who will greet them, obtain their electronic consent on the iPad and show them how to complete the questionnaires on the iPad.

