### Patient perceptions

Patient ratings of feasibility and acceptability will be assessed in several ways. The first is by the proportion of eligible patients approached who completed baseline and at least one set of follow-up PROMs data. If 60% of patients meet this requirement, the study will be deemed feasible and acceptable overall.

Data on individual patient measures of feasibility and acceptability will also be collected. In the first set of two triage questionnaires, all questions are mandatory, but with the second set of three questionnaires, patients are not required to answer all questions. Metadata from the patients who are triaged to complete the second group of questionnaires will be collected to provide an estimate of the mean time taken to complete the PROMs questionnaires and the amount of missing data (providing a second measure of patient acceptability for those who completed all five questionnaires). If patients take more than 30 min to complete the five questionnaires, they will be considered as not having met this acceptability criteria. Additional measures will include changes in baseline and follow-up scores and the proportion of patients who: ‘agree or strongly agree’ that the PROMs were easy to complete and that the questions they completed measured issues they considered important to their QoL (online supplemental appendix 3a). Semistructured interviews with patients will also assess feasibility and acceptability through the following main question themes: enjoyment of completing the PROMs; changes in patient–clinician communication; changes in their management; and improvements or challenges they found in the processes.

10.1136/bmjopen-2022-066852.supp3Supplementary data

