### Ethics and dissemination

#### Ethics and consent

Original ethics approval was obtained from St Vincent’s Hospital Human Research Ethics Committee (HREC) on 19 September 2019 (2019/ETH10558). This approval included site authorisation for the following two project sites:

Sydney Melanoma & Surgical Oncology, MIA, Poche Centre.Sydney Melanoma & Surgical Oncology, RPAH, Camperdown.

Amendments to the original protocol were accepted by St Vincent’s HREC on 8 June 2022.

Consent is obtained electronically on the iPad from all patients prior to commencing the questionnaires, while clinical staff signed written consent forms. All participants who complete end-of-study surveys or interviews will sign additional written consent forms. There are no foreseeable additional harms, risks or costs associated with taking part in this study that are not outlined in the PIS. It is possible some patients may experience short-term distress while answering the questionnaires. If a patient does not wish to answer a question, they may skip it and go to the next question (if they are completing the second set of questionnaires), or immediately stop completing the questionnaires (if they are completing the first set of questionnaires, where all questions are mandatory). A melanoma clinical nurse consultant and/or treating clinician will be available to talk with a distressed patient if their distress continues once they have stopped completing the questionnaire. Patients are free to withdraw from the study at any time. Clinicians may experience frustration with having to review patient summary scores from the questionnaires if they are particularly busy.

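### The second patient acceptability measure names two populations, and its 30-minute rule has no outcome for a triaged patient who does not finish

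*Protocol article*

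**What the plan says.** In the protocol article, patient perceptions are the first of the three components of the primary outcome (Outcomes). Under Patient perceptions, the study as a whole is deemed feasible and acceptable if 60% of the eligible patients who were approached provide baseline data and at least one follow-up set.

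A further measure then follows for patients with a Distress Thermometer score of 4 or more, who go on to three more questionnaires. Its source is stated as "Metadata from the patients who are triaged to complete the second group of questionnaires will be collected". From these data come the mean completion time and "the amount of missing data (providing a second measure of patient acceptability for those who completed all five questionnaires". The failure rule is: "If patients take more than 30 min to complete the five questionnaires, they will be considered as not having met this acceptability criteria".

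Other statements bear on who finishes:

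- Patient perceptions: first-set items are mandatory, but "with the second set of three questionnaires, patients are not required to answer all questions".
- Patient recruitment process: patients are asked to arrive 30 min "earlier for their scheduled appointment to allow time to complete the questionnaires".
- Interventions: all five questionnaires are expected to take under 30 min.
- Ethics and consent: a patient unwilling to answer an item may skip it in the second set, "or immediately stop completing the questionnaires (if they are completing the first set of questionnaires, where all questions are mandatory".
- Secondary outcomes: completion time and the number of second-set items answered are recorded, with no restriction to patients who finish.

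**The concern.** One sentence points to two groups: everyone triaged, and those who completed all five questionnaires. They differ by exactly the patients who found the second set too long or too unwelcome to finish. If those patients are left out, an acceptability measure is computed after removing people for whom acceptability is most in doubt.

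The time rule has the same weakness in another form. It needs a completion time, and a patient who never finishes does not have one.

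The document gives reason to expect some unfinished sessions. The early-arrival slot equals the time limit. At the first visit, the arrival also includes a last chance for questions, electronic consent and a demonstration of the iPad. Results must be ready for the consultation that follows. The pilot's results are meant to inform expansion to all the institute's melanoma clinics, so the share of distressed patients who can manage the full battery is of practical interest.

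**Working it through.** **Reading the passages together.** Completing all five questionnaires can be understood in three ways.

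1. *Every item answered.* This cannot be meant. First-set items are mandatory and second-set items may be skipped, so missing data would be zero by definition.
2. *Reached the end of all five, with skips allowed.* This is the literal reading. A patient who stops part-way leaves both the missing-data measure and the time measure.
3. *Routed to five questionnaires rather than two.* This is the generous reading. A patient who stops part-way contributes unanswered items to the missing data. The time rule still has no outcome for that patient, because it refers to time taken to complete.

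The gap in the time rule therefore exists under readings 2 and 3. The gap in the missing-data measure exists only under reading 2.

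**Number triaged.** The inputs are the target of 50 patients and the assumed 30% distress rate (Eligibility criteria and sample size). 50 × 0.30 = 15. The article states about 17, which would be 17/50 = 34%. The difference does not affect this point, so both values are carried.

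**Direction.** Let n be the number triaged, s the number who do not finish, and l the number who finish after 30 min.

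- Share meeting the limit among finishers: (n − s − l)/(n − s)
- Share meeting the limit among all triaged: (n − s − l)/n

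The numerators are equal and n − s ≤ n, so the first share is never below the second. The gap is (n − s − l)/(n − s) × s/n. With l = 0 it is s/n, so each non-finisher is worth 1/17 = 5.9 to 1/15 = 6.7 points, and slightly less when some finishers are late.

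**Illustrations.** The values of s and l are assumptions, with one session per patient.

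| n | s | l | Among finishers | Among all triaged |
|---|---|---|---|---|
| 17 | 0 | 1 | 16/17 = 94% | 16/17 = 94% |
| 15 | 1 | 0 | 14/14 = 100% | 14/15 = 93% |
| 15 | 2 | 0 | 13/13 = 100% | 13/15 = 87% |
| 17 | 1 | 1 | 15/16 = 94% | 15/17 = 88% |
| 17 | 3 | 1 | 13/14 = 93% | 13/17 = 76% |

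If nobody stops, there is no difference.

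**The case against.** The strongest reply is that the sentence begins with triaged patients, and the closing phrase may only separate those given five questionnaires from those given two. Secondary outcomes supports this, since second-set items answered are recorded without limiting the record to finishers. This stands against a reader's inference that missing data are assessed only in completers: the document does not say so unambiguously. It does not rescue the time rule, which has no result for a non-finisher on either reading.

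Second, patients who stop are not lost to every measure. The 60% criterion is taken over eligible patients approached, and Quantitative analysis also reports consent, participation and completion rates. A reader might conclude that first-set stoppers are missed entirely. That is not supported. They may be absent from the second-set metadata, which is a separate gap, but the other measures may count them. Those measures are no full substitute, because a patient can abandon one follow-up session and still satisfy the 60% criterion through another.

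Third, no passage says that patients are called in before finishing, and the article expects all five questionnaires to fit within 30 min. Interruption is therefore a plausible route and not a documented one. A patient who finishes late does fail the rule as written.

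Fourth, classifying unfinished sessions might be left to an analysis plan. That would answer a complaint about missing detail. Here the protocol itself states a population and a failure rule, and the two do not fit together.

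**Conclusion.** The point holds in a limited form. The second acceptability measure is given two populations, and its 30-minute rule can fail only patients who finish. Treating non-finishers as outside the measure can only leave the share within the limit unchanged or raise it. On the literal reading these patients also drop out of the missing-data measure.

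The size depends on a stopping rate that the documents do not give. Under the assumption of 15 to 17 triaged patients with one session each, it is about 6 to 7 points per non-finisher.

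A reader might go further and infer that the study's overall acceptability finding is biased. The documents do not support that. No pass proportion is attached to this measure, the overall decision rests on the 60% criterion, and that criterion and the completion rates may capture some of the same patients. The effect is confined to this part of the primary outcome. It is worth correcting because it runs in one direction and costs little to remove.

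**What to change.** In Patient perceptions:

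- Replace the reference to patients who completed all five questionnaires with all triaged sessions, meaning those with a Distress Thermometer score of 4 or more, as the single denominator.
- State that an unfinished session counts as not meeting the 30-minute criterion.
- State that its unanswered second-set items count as missing.
- Where session logs allow, report stops during the first set separately, over all sessions started.

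The cost is wording. The metadata for triaged sessions and the count of second-set items answered are already planned, and no visit or instrument is added. The first-set report depends on the software logging abandoned sessions, which the article does not confirm. The downside is that the acceptability figure may come out slightly lower.

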**Methods and analysis:**

A minimum of 50 patients and 5 clinicians will be recruited to this prospective, longitudinal pilot study (ePROMs-MELanoma). The study uses a mixed-methods approach (quantitative PROMs questionnaires and end-of-study surveys with qualitative interviews) and commenced in May 2021 in surgical and medical melanoma clinics at two sites in metropolitan Sydney, Australia. The primary outcomes are measures of feasibility and acceptability, comprising descriptive questionnaire completion statistics, and proportion of patients who reported that these PROMs were easy to complete and measured items they considered important. Clinician and clinic staff views will be canvassed on the appropriateness of these PROMs for their patients, change in referral practice and uptake and incorporation into routine practice. Secondary aims include measurement of improvements in patients’ emotional and physical health and well-being, and utility of real-time data capture and clinician feedback. All participants will complete the Distress Thermometer and EQ-5D-5L questionnaires in the clinic using a tablet computer at baseline and two to three subsequent follow-up appointments. Participants who report a score of 4 or higher on the Distress Thermometer will be triaged to complete an additional three questionnaires: the QLQ-C30, Depression, Anxiety and Stress Scale and Melanoma Concerns Questionnaire-28. Results will be generated in real time; patients with psychosocial distress or poor quality of life will discuss possible referral to appropriate allied health services with their clinician. Thematic analysis of interviews will be conducted.

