### Eligibility criteria and sample size

Patients are eligible to participate if they are aged 18 or over, have received a diagnosis of Stage III melanoma at least 1 month earlier, are under the care of melanoma clinicians at MIA or RPAH, and have sufficient English and cognitive ability to comprehend study materials, provide informed consent and participate in the study. Clinicians, including surgical oncologists, medical oncologists, dermatologists and melanoma general practitioners, are eligible to participate if they are currently treating and managing patients with stage III melanoma at MIA or RPAH.

This research project has experienced substantial delays to recruitment due to research staff being unable to enter clinic sites during COVID-19. In April 2022, the decision was made to reduce the initial recruitment target of 100–50 patients, so that the trial may be completed before external funding expires (the minimum number of clinician participants is five). The target reduction is justified on the basis that this project is a non-randomised feasibility pilot study. Assuming 30% of stage III melanoma patients have levels of distress that indicate the need for clinical intervention,^13^ we would expect to identify approximately 17 patients within our sample who will be triaged for discussion of referrals to support services. This number is considered sufficient to inform a decision on whether or not to proceed to a larger-scale trial with additional sites.

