#### Interventions

The study questionnaires will be repeated at subsequent regularly scheduled follow-up appointments with their clinicians, with a minimum of 2 months between patient completion of questionnaires. Questionnaires will be administered at baseline, with a minimum of two and a maximum of three, follow-up time points. iPads were chosen as the delivery platform because they are portable, have a user-friendly interface, are capable of hosting software that can automatically generate reports and associated documents and are a secure format for data management as they are encrypted by default. All questionnaires used in this study have been validated in previous studies.

At each visit, all patients will be required to complete two short questionnaires that are used to assess their psychosocial distress and quality of life: (1) the National Comprehensive Cancer Network’s Distress Thermometer and Problem List for Patients^19^ and (2) EuroQoL’s EQ-5D-5L (five dimensions, five levels) and Visual Analogue Scale.^20^ Patients who score above the clinical cut-off score on the Distress Thermometer (4 or above) will be triaged to complete an additional three questionnaires: the Melanoma Concerns Questionnaire (MCQ-28),^21^ the Depression, Anxiety and Stress Scale (DASS-21)^22^ and the European Organisation for Research and Treatment of Cancer (EORTC)’s Quality of Life Questionnaire - Cancer (QLQ-C30).^23^ These additional questionnaires will provide more detailed information about potential areas of support needs. Completion time for all five questionnaires is expected to be less than 30 min. All questionnaires are provided in online supplemental appendix 1.

10.1136/bmjopen-2022-066852.supp1Supplementary data

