After all rounds of patient questionnaires (baseline plus 2–3 follow-up rounds per patient) have been completed, all patients, clinicians and clinic staff involved in the project will be asked to complete an electronic survey providing quantitative and open-ended assessments of their experiences with the PROMs questionnaires. In addition, approximately 20% of patients (10 patients), all study clinicians and clinic staff with major involvement in the study will be invited by the research team to participate in a short (10 min) confidential interview to expand on their survey responses. Patients will be purposively sampled to maximise response variation, based on a range of individual views and experiences as identified from their survey results. Patients who complete an interview will be offered a US$30 gift card to thank them for their time, while clinicians and clinic staff who participate in an interview will not be reimbursed. Figure 1 provides a study flow chart from the patient’s perspective and figure 2 provides the study overview from the clinician’s perspective.

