### Data analysis and statistical methods

#### Quantitative analysis

Participant demographics and characteristics will be summarised for all participants using means and SD. In addition, the consent, participation and completion rates will be analysed. Consent will be defined as agreeing to participate in the study and returning a signed consent form; participation, as completing some of the components of the study; and completion, as completing all components of the study. Specifically, the proportion of eligible participants who completed the project tasks will be assessed to determine whether the inclusion of ePROMs are acceptable for patients undergoing follow-up treatment for stage III melanoma. Descriptive statistics will be reported for QoL and other questionnaire domain scores at baseline and follow-up time points. Referral and referral uptake rates will also be calculated. The small sample size of 50 for this pilot study precludes any subgroup analysis. Linear mixed effects modelling will be used to account for repeated measures and differential time points among participants. This is similar to analysis of longitudinal data from a clinical trial where measurements at follow-up time points are missing.^27^

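### The ease and importance proportions pool patients who completed two questionnaires with patients who completed five, and the bar on subgroup analysis, read literally, prevents separating them

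*Protocol article*

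**What the plan says.** Under Interventions, at each visit "all patients will be required to complete two short questionnaires", namely the Distress Thermometer and the EQ-5D-5L. The next step depends on the score: "Patients who score above the clinical cut-off score on the Distress Thermometer (4 or above) will be triaged to complete an additional three questionnaires", which are the MCQ-28, DASS-21 and QLQ-C30. The same section says that after the last round "all patients, clinicians and clinic staff involved in the project will be asked to complete an electronic survey", so triaged and untriaged patients answer the same kind of end-of-study survey.

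Patient perceptions then defines, as additional measures, the proportion of patients in agreement or strong agreement that "the PROMs were easy to complete and that the questions they completed measured issues they considered important to their QoL". The abstract gives this more weight and names among the primary outcomes the "proportion of patients who reported that these PROMs were easy to complete and measured items they considered important". Neither place separates patients by which questionnaires they completed.

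Quantitative analysis adds: "The small sample size of 50 for this pilot study precludes any subgroup analysis".

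Patient perceptions also contains measures confined to triaged patients: mean completion time, a 30-minute criterion for the five questionnaires, and the amount of missing data in the second set.

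**The concern.** One proportion answers for two experiences that differ in length and content. A patient who never reached the cut-off has no view on the burden of five questionnaires or on whether the MCQ-28 asks about the right things. Only triaged patients can say that, and they are the distressed patients whom the pathway is meant to help.

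This matters because the Introduction links favourable pilot results to expansion across all of the institute's melanoma clinics, and the strengths list presents the triage system and the first use of the MCQ-28 as features of the study. If most respondents saw only the two short forms, a favourable pooled figure could coexist with an unfavourable view among those who saw all five. The split that would reveal this is the one that the subgroup sentence, taken at its word, rules out.

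**Working it through.** **Inputs.** Sample size 50 (Quantitative analysis). Distress rate 30% (Eligibility criteria and sample size, "Assuming 30% of stage III melanoma patients have levels of distress that indicate the need for clinical intervention"). The plan's own expected number identified is about 17 (same section). Patients have three or four assessments: baseline plus two or three follow-ups (Interventions). Agreement rates are not given in the article, so those below are assumptions. All 50 patients are assumed to answer the survey.

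**Step 1: the plan's figure.** 50 × 0.30 = 15, against the stated 17. Seventeen is 34% of 50, or 30% of about 57 (17 / 0.30 = 56.7). The gap of two patients does not affect this point; both counts are carried forward.

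**Step 2: how far pooling can mask.** With *t* triaged patients, agreement *a* among the untriaged and *b* among the triaged:

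pooled = [(50 − *t*) × *a* + *t* × *b*] / 50

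| Assumed *a*, *b* | *t* = 15 | *t* = 17 |
|---|---|---|
| 100%, 0% (extreme) | 35/50 = 70% | 33/50 = 66% |
| 90%, 40% | (31.5 + 6)/50 = 75% | (29.7 + 6.8)/50 = 73% |
| 80%, 40% | (28 + 6)/50 = 68% | (26.4 + 6.8)/50 = 66% |

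**Step 3: triage repeats at each visit.** Step 2 counts triage once per patient. If the same patients are distressed every time, the ever-triaged share stays at 30%. If visits were independent (an assumed upper bound), it would be 1 − 0.7³ = 66% over three visits and 1 − 0.7⁴ = 76% over four. The extreme row of the table would then fall to 34% and 24%. So the patients who see five questionnaires need not be a minority, and masking is strongest when distress is persistent.

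**Step 4: what a split would give.** Exact (Clopper-Pearson) 95% intervals:

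- five-questionnaire group: 12/15 (80%), 52% to 96%; 9/15 (60%), 32% to 84%
- two-questionnaire group: 28/35 (80%), 63% to 92%
- pooled: 40/50 (80%), 66% to 90%

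**Step 5: why completion should not be split the same way.** A patient who stops after baseline has one chance to be triaged; a completer has three or four. Assume 70% completion regardless of distress, 30% triage independently at each visit, and three visits for completers.

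- Ever triaged: completers 0.70 × 0.657 = 0.460; dropouts 0.30 × 0.30 = 0.090. Completion = 0.460 / 0.550 = 84%.
- Never triaged: completers 0.70 × 0.343 = 0.240; dropouts 0.30 × 0.70 = 0.210. Completion = 0.240 / 0.450 = 53%.

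The gap is entirely an artefact of the classification.

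**The case against.** The strongest reply is that the intervention is a single triage pathway, chosen to spare undistressed patients a long survey, and that routine care would use the same pathway. Acceptability across everyone who enters it is then a legitimate target. That stands, and it is why the pooled figure should be kept.

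The article also already examines triaged patients separately, through time, the 30-minute criterion and missing data. This is true and useful, but these are process measures. None shows whether patients who saw the longer set found it easy or its content important.

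The importance item is limited to the questions each patient completed, so untriaged patients are not rating the MCQ-28. That also stands. It means that patients rate different content within one numerator, and the ease item carries no such limit.

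The subgroup sentence may be aimed only at comparative analyses, since the authors themselves plan triaged-only measures. That is plausible, but the word *any* invites the wider reading. The patient survey form (supplemental appendix 3a) is not shown and may ask about each questionnaire; this cannot be checked.

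A reader might go further and infer that the full set could be formally declared acceptable by patients who never saw it. The article does not support that. Ease and importance have no pass mark. The only overall declaration is the 60% completion rule, which concerns the study as a whole.

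**Conclusion.** The point holds as a limit on interpretation. As defined, the ease and importance proportions cannot show how patients who completed the QLQ-C30, DASS-21 and MCQ-28 regarded them. With 15 of 50 triaged, the pooled figure could reach 70% with no agreement among them (66% with 17). This rests on the plan's 30% rate, on triage counted once per patient and on full survey response; it weakens if more patients are triaged at some visit. The agreement rates are illustrative, so the calculation shows what pooling could conceal and does not predict the result. No threshold or go/no-go rule is compromised.

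**What to change.** - **Patient perceptions:** report ease and importance descriptively by whether the patient ever completed the second set, with counts and exact confidence intervals, alongside the pooled figure.
- **Quantitative analysis:** state that the subgroup exclusion applies to comparative or inferential analyses and not to this tabulation.
- **Reporting:** limit any statement on the acceptability of the five-questionnaire set or the MCQ-28 to patients who completed it.
- **If completion is also split:** use triage status at baseline among enrolled patients, not ever versus never triaged, and leave the 60% rule's denominator (eligible patients who were approached) unchanged.

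The cost is some wording and an extra column or two in the tables; triage status follows from the Distress Thermometer score already collected at each visit. The drawback is imprecision in a group of about 15 to 17, as the intervals above show.
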